### Sample Size Determination and Randomization

An a priori power analysis was performed to estimate the required sample size using G*Power 3 [40,41] based on the study’s primary outcome, the CAT [37]. These were conducted for the more straightforward two-sample *t* test procedure, as this is known to yield a conservative assessment of power. For a two-sided test at α=.05, a total sample size of 200 results in 80% power for a standardized effect size of 0.4 and 94% power for an effect size of 0.5. Increasing the sample size to 250 raises the power to 88% and 98%, respectively. A sample size of 250 provides 79% power to detect a standardized effect size of 0.35. To account for up to 20% potential dropout over time, we aim to enroll 300 participants (targeting 150 Black and 150 White participants). Once participants provide consent, REDCap (Research Electronic Data Capture) [40] will randomize them into 1 of 2 experimental arms: (1) PCD tool (ie, facilitated enrollment for PCD tool intervention) or (2) usual care (ie, email invitation only for PCD tool). We will use stratified random sampling to ensure equal representation of Black and White participants in each arm. Stratified randomization prevents an imbalance of racial representation between arms.

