### Randomization of Study Participants

#### Allocation Process

An allocation table was created using R to develop a block randomization scheme to balance arms and stratification by race. The block randomization scheme was then incorporated into the REDCap [40] system. Randomization is stratified by race in a 1:1 ratio, ensuring that we oversample Black participants based on population demographics. Blinding does not occur for either the participant or the study team. Participants are invited to join a communication study but are not told whether the study will focus on their use of the PCD tool.

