#### Data Collection

We will use self-reported surveys to assess the differences in patient-provider communication and patient activation between the PCD tool and usual care arms and by race (Black and White). The primary outcome measure is patient-provider communication assessed using the CAT [37] after the visit. The 15-item measure is unidimensional and has high internal consistency (Cronbach α=.96), with readability at or below an eighth-grade level [37]. The psychometric properties of CAT were tested in a diverse sample. The testing revealed that the instrument has content and construct validity and reliably [37] measures patients’ perceptions of physicians’ interpersonal communication skills. We will examine individual items and the proportion of items with top ratings. The CAT was designed to be administered directly following a visit and is not yet validated in a retrospective context. Therefore, we will use the Clinician and Group Consumer Assessment of Healthcare Providers and Systems (CG-CAHPS) survey [47,48] communication composite questions validated for patients’ perceptions of communication with their provider within the past 12 months as the baseline communication measure. The outcome will be the CAT adjusted for the baseline CG-CAHPS score.

We will use the 13-item PAM [38] to assess changes in the secondary outcome and patient activation, examining the change in pre- and postvisit assessments. Conducted with a nationally representative sample, psychometric testing revealed that the 13-item PAM questionnaire yielded a strong Rasch person reliability score between .85 (real) and .87 (model), and the Cronbach α value was acceptable at .87 [38].

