We will collect the following independent variables in the previsit survey: CG-CAHPS communication composite [47], Patient-Reported Outcomes Measurement Information System (PROMIS) Global Health [49], health literacy [50], technology use or technology acceptance [51], and sociodemographic characteristics. We will measure previsit patient-provider communication using the communication composite of the CG-CAHPS survey [48]. The CG-CAHPS communication composite has high internal consistency (Cronbach α=.89) [47], which was determined using a nationally representative sample of over 21,000 patients from 450 US practice sites. We will assess participants’ perceptions of their global health using the PROMIS 10-item Global Health Short Form, which includes scores on global physical health and global mental health. The PROMIS 10-item Global Health Short Form scales had internal consistency reliability coefficients of 0.81 for global physical health and 0.86 for global mental health in a large national survey [49]. Technology use or technology acceptance will be collected using the Health Information National Trends Survey 5, Cycle 1 [51]. Participants will report health literacy using a validated one-item tool [50]. Sociodemographic characteristics and other hypothesized predictors of the outcome measures include income, age, sex, gender identity, health insurance status, educational attainment, number and type of chronic conditions, and length of relationship with primary care provider (in months or years).

We will monitor the use of the PCD tool in 3 ways. First, we will assess whether those in the PCD tool arm completed their profile before their appointment. Second, for participants in the usual care arm, we will determine if they created a profile after they entered the study, as all patients in the academic medical center have access to the PCD tool. Third, we will assess whether any of the care team members reviewed the participant’s PCD tool profile within one day before the appointment and on the day of the appointment. Figure 3 displays the Randomized Controlled Trial Standard Protocol Items: Recommendations for Interventional Trials (SPIRIT) [39] including an overview of study time points, intervention, and assessments of the randomized controlled trial.

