#### Analysis

The trial will evaluate the differences between the arms for change in PAM scores [38] and the CAT score (a postvisit measure) [37], adjusting for the CG-CAHPS score (a previsit measure). The research team will also assess differences in pre- and postvisit patient activation and postvisit patient-provider communication by race. Our primary analysis is an intention-to-treat (ITT) analysis, where every randomized participant is analyzed in the group to which they were randomly assigned [52,53]. Chi-square tests for categorical variables and independent sample *t* tests for continuous variables will be used to examine the differences between the groups at baseline and postvisit. Descriptive statistics (means and standard deviations) will be conducted for the following variables: age, CG-CAHPS communication composite score [47], and PROMIS 10-item Global Health Short Form [49]. Frequencies will be calculated for sex, gender identity, education, marital status, employment status, income, health insurance coverage and type, difficulty paying bills, health literacy, internet use, internet access, internet access location, and internet access device. We will also extract data from each participant’s EHR to calculate their Charlson Comorbidity Index [54] as a measure of morbidity. Previsit assessment of communication using CG-CAHPS [47] as a control variable and postvisit assessment of communication using the CAT [37] will be tested within and between groups using linear regression, controlling for covariates. A linear regression model will be used to determine the factors that predict changes in patient-provider communication and patient activation, controlling for covariates.

However, we expect that there will be some crossover and noncompliance between arms. For example, some individuals randomized to the PCD tool arm may not complete a profile, and some individuals not randomized to enroll in the PCD tool may create a profile. To overcome this limitation, we will conduct additional analyses that account for noncompliance and estimate the effect of the treatment-on-the-treated (TOT) instead of the ITT [55,56]. TOT is sometimes referred to as the local average treatment effect or as a *per-protocol* analysis. We will identify this using a two-stage least squares regression [57,58]. The first stage of the model estimates whether a person used the PCD tool during the follow-up period.

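### Postvisit arm differences are tested both by an unadjusted t test and by a CG-CAHPS-adjusted regression, with no ranking; race, the randomization stratum, and baseline PAM are not named as terms in the arm comparisons

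*Protocol article*

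**What the plan says.** All references are to the protocol article.

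- **Analysis.** ITT is the primary analysis, which fixes who is analysed and in which group. The next sentence provides chi-square tests for categorical variables and says that independent-sample t "tests for continuous variables will be used to examine the differences between the groups at baseline and postvisit". Later in the same paragraph, postvisit CAT, with CG-CAHPS as control variable, is tested within and between groups "using linear regression, controlling for covariates". One threshold, P<.05, applies throughout. PAM is described as a change score.
- **Data Collection.** "The outcome will be the CAT adjusted for the baseline CG-CAHPS score". Study Design and the opening sentence of Analysis agree with this.
- **Allocation Process.** "Randomization is stratified by race in a 1:1 ratio".
- **Predictors and adjustment factors.** Data Collection states: "Sociodemographic characteristics and other hypothesized predictors of the outcome measures include income, age, sex, gender identity", and goes on to insurance, education, chronic conditions and length of the provider relationship. Study Objectives names age, gender and other patient factors as adjusters, and race as a possible effect modifier.
- **Provider and center.** The end of Analysis plans SAS GLM and MIXED to handle provider and center heterogeneity.

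**The concern.** CAT is a continuous postvisit measure, so the t-test sentence covers it. The article therefore contains two tests of the arm difference in the primary outcome, at the same threshold, and does not say which one decides the trial. They can disagree. The t test also does not estimate the outcome as Data Collection defines it, because it ignores CG-CAHPS.

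Two related points concern the form of the regression. When randomization is stratified on a factor that predicts the outcome and the analysis leaves that factor out, the standard error is overstated. Race is the stratum here, and no sentence names it as a term in the main arm comparison. For PAM, a simple comparison of changes does not make the best use of a baseline value that is already collected.

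At stake are precision and one clear primary test. Randomization protects every one of these comparisons from systematic bias.

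**Working it through.** **1. The plan's own figures.** Sample Size Determination and Randomization bases power on an unadjusted two-sample t test, two-sided α=.05, and calls this conservative. Exact noncentral t, equal arms:

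| Total N | Effect (SD) | Stated | Recomputed |
|---|---|---|---|
| 200 | 0.4 | 80% | 80.4% |
| 200 | 0.5 | 94% | 94.0% |
| 250 | 0.4 | 88% | 88.3% |
| 250 | 0.5 | 98% | 97.6% |
| 250 | 0.35 | 79% | 78.7% |

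All five reproduce. The sample size does not depend on covariate adjustment, so naming an adjusted model as primary needs no more participants.

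**2. CG-CAHPS adjustment against the t test.** The correlation r between CG-CAHPS and CAT is not given; I assume 0.3 to 0.6. The standard error (SE) ratio, adjusted to unadjusted, is √(1 − r²). Power is for N=250 and an effect of 0.35 SD, with the effect divided by that ratio.

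| r | SE ratio | SE reduction | Power |
|---|---|---|---|
| 0 (t test) | 1 | 0% | 79% |
| 0.3 | √0.91 = 0.954 | 5% | 82% |
| 0.5 | √0.75 = 0.866 | 13% | 89% |
| 0.6 | √0.64 = 0.800 | 20% | 93% |

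**3. Adding race.** With a 50:50 split and an assumed Black-White CAT difference of δ SD, race explains R² = (δ/2)².

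- δ = 0.3: R² = 0.0225, √(1 − 0.0225) = 0.989, SE reduction 1.1%.
- δ = 0.5: R² = 0.0625, √(1 − 0.0625) = 0.968, SE reduction 3.2%.

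A simulation of race-stratified 1:1 randomization checks this (N=248; 10,000 null replicates and 4,000 with effect 0.35 per scenario; both R² columns assumed):

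| Race R² | CG-CAHPS R² | Type I error, arm + CG-CAHPS | Type I error, race added | Power, arm + CG-CAHPS | Power, race added |
|---|---|---|---|---|---|
| 0 | 0.10 | 0.050 | 0.050 | 82.5% | 82.5% |
| 0.02 | 0.10 | 0.047 | 0.050 | 81.8% | 82.3% |
| 0.05 | 0.20 | 0.044 | 0.049 | 86.1% | 87.5% |
| 0.10 | 0.20 | 0.036 | 0.050 | 88.6% | 90.4% |
| 0.05 | 0.30 | 0.042 | 0.050 | 91.9% | 92.9% |

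Omitting race makes the test conservative and costs 0 to 2 power points.

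**4. If either test could decide.** Under the null the two statistics correlate at about √(1 − r²). The bivariate normal probability that at least one reaches P<.05 is 6.4% (r=0.3), 7.3% (0.5) and 7.8% (0.6). The simulation in step 3, taking the t test or the model with race, gives 6.4% to 7.4%.

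**5. PAM.** Let ρ be the correlation between previsit and postvisit PAM, not given in the article, and assume equal variances. A change score has variance proportional to 2(1 − ρ); adjustment for baseline gives 1 − ρ². The SE ratio is √[(1 − ρ²)/(2(1 − ρ))] = √[(1 + ρ)/2].

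- ρ = 0.5: √0.75 = 0.866, SE reduction 13%.
- ρ = 0.7: √0.85 = 0.922, SE reduction 8%.
- ρ = 0.8: √0.90 = 0.949, SE reduction 5%.

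**The case against.** The best defence is that the adjusted comparison is already the plan. Study Design, Data Collection and the opening of Analysis all say that the CAT is adjusted for CG-CAHPS. The sample size section treats the t test as a stand-in for power, and the software sentence names modelling procedures. On that reading the t and chi-square tests merely introduce the descriptive lists. This is a plausible account of the intent, and CG-CAHPS adjustment is indeed not new. But the t-test sentence says postvisit, follows the ITT sentence directly, and is nowhere called descriptive. The word groups is undefined and the preceding text also mentions race, but after that ITT sentence arms is the natural reading.

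A reader might infer that the plan leaves race out. The documents do not support that. Study Objectives sets out to account for Black-White differences and tests effect modification by race, outcomes are assessed by race, and imputation is stratified by race. The list in Data Collection is open-ended, the lists in Analysis are descriptive, and the covariates of the regression are not enumerated. Race is unnamed in the main arm comparison, not excluded. Likewise, baseline PAM must enter the effect-modification model of the second aim and could be among the unnamed covariates. A complete covariate list may properly sit in an analysis plan that is not shown.

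A reader might also infer a false-positive rate of 6% to 8%. That requires a rule that either test may declare success, and no sentence states one.

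Finally, a model with only arm, race and CG-CAHPS would contradict the adjustment for age, gender and other patient factors and the handling of providers and centers. That objection stands, so the fix keeps those terms.

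**Conclusion.** The point holds as a minor fault in stated methods. The article gives two unranked tests of the postvisit arm difference, and one of them does not match its own definition of the primary outcome. It does not name the randomization stratum in the main arm comparison, and it states no baseline adjustment for the PAM change.

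Against the t test, the adjusted SE is about 5% to 20% smaller, given an assumed CG-CAHPS to CAT correlation of 0.3 to 0.6; this gain is already available in the planned regression. Naming race adds about 1% to 3% in SE for an assumed difference of 0.3 to 0.5 SD. The PAM gain of 5% to 13% assumes a pre-post correlation of 0.5 to 0.8. None of these inputs is in the article. No result here indicates bias, and the sample size is unaffected.

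**What to change.** In Analysis:

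1. State that the postvisit t and chi-square tests are descriptive only.
2. Name the primary ITT test as the regression of postvisit CAT on arm, race stratum and baseline CG-CAHPS. Keep the age, gender and other patient factors from Study Objectives and the provider and center terms already planned.
3. Analyse PAM by the same model, with postvisit PAM as outcome and baseline PAM as the baseline covariate in place of CG-CAHPS. Align the wording on PAM change in Data Collection.

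The cost is a few sentences. No new data are needed, because race, CG-CAHPS and previsit PAM are all collected, and no larger sample is required. The article reports that analysis was completed in May 2020, so the results report should state which test was primary and whether that was fixed beforehand. A model changed now should be labelled as such.

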##### Enrollment Process for PCD Tool Facilitation

The facilitation enrollment process includes a description of the PCD tool, followed by the study team member either assisting the participant in registering a PCD tool account using the link to the PCD tool site sent by email or describing how to register a PCD tool account through the patient’s portal. Next, the study team member will review the types of *stories* to share, in the domains of (1) information about me, (2) issues related to my care, (3) my upcoming visit agenda, and (4) barriers to care, to highlight all of them as important pieces of data. In addition, the study team member will share how to upload a picture to the profile. After completing the instructions, the study team member will share that the completed profile would then be available to the care team. The participant can then view how their profile would appear in their EHR via the one-screen summary.

The research team member will document the type of PCD tool facilitation (ie, email link only, over the telephone, or in person) for each participant and take field notes of each facilitation experience. Approximately 1 week before the primary care visit, the research staff will recontact the participant either by telephone or email up to three times. The research staff will thank the participant for being part of the study and inquire if they have questions regarding completing or updating their PCD tool profile. Research staff will also remind the participant to complete the profile, if it is not yet finished.

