The second stage will identify the causal impact of using the PCD tool on outcomes (patient activation and patient-provider communication). To do this, we will model the predicted use of the PCD tool from stage 1 in the stage 2 model and use the results of this coefficient to interpret how the PCD tool impacts patient activation and patient-provider communication.

A missing value analysis will be conducted on the final data set to determine whether data were missing completely at random, missing at random, or missing not at random [59,60]. To reduce the likelihood of missing data biasing our results, we will use multiple imputation by chained equations to fill in missing data stratified by race [59]. The imputation algorithm will include participant demographics and clinical characteristics. Multiple imputation has been increasingly applied to clinical research to address the common problem of incomplete data sets [60].

For all aims, statistical analysis will be completed using SAS [61] procedures GLM and MIXED to assess and account for possible provider and center heterogeneity. A *P* value of <.05 is considered statistically significant.

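### With tool use expected in both arms, the two-stage least squares analysis estimates the complier effect (LATE), not the treatment-on-the-treated or per-protocol effect the protocol names; a second stage run by hand would also leave its standard errors slightly off

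*Protocol article*

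**What the plan says.** In the Analysis section of the protocol article, the main comparison is fixed first: "Our primary analysis is an intention-to-treat (ITT) analysis". Because noncompliance is expected, additional analyses are to "estimate the effect of the treatment-on-the-treated (TOT) instead of the ITT". The target is then given other names: "TOT is sometimes referred to as the local average treatment effect or as a" per-protocol analysis. On the estimator: "We will identify this using a two-stage least squares regression". On its stages: "The first stage of the model estimates whether a person used the PCD tool during the follow-up period", and the second stage will "model the predicted use of the PCD tool from stage 1 in the stage 2 model and use the results of this coefficient".

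The same section expects noncompliance in both directions: some of the PCD tool arm will not complete a profile, and some of the usual care arm will create one. Two other sections agree. Under Usual Care Arm, these participants receive the automatic email that invites every patient to the tool. Under Data Collection, all patients have access, and profile creation in usual care will be tracked.

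The section closes with a general software statement, "For all aims, statistical analysis will be completed using SAS [61] procedures GLM and MIXED", whose stated purpose is to deal with provider and center heterogeneity. Study Design Innovations repeats that the TOT analysis will give the causal effect of using the tool.

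**The concern.** TOT, LATE and per-protocol are three different quantities. TOT is the average effect in everyone who used the tool, in either arm. LATE is the average effect in compliers, that is, those who use the tool if facilitated and otherwise would not. A per-protocol contrast compares people who followed their assignment, and these groups are partly self-selected.

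With one-sided noncompliance, TOT and LATE coincide. Here noncompliance is two-sided by the protocol's own account, so they need not. The named estimand and the named estimator therefore do not match. A reader would apply the result to all tool users, or take it for a comparison that randomization does not protect.

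A smaller issue is how the second stage is run. If predicted use is entered in an ordinary regression, the printed standard error is not the 2SLS standard error.

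**Working it through.** **The protocol's own figures.** The only computable figures are the t-test powers under Sample Size Determination and Randomization, and they reproduce (noncentral t): N=200, 0.804 and 0.940 (stated 80%, 94%); N=250, 0.883, 0.976 and 0.787 (stated 88%, 98%, 79%). They concern the ITT comparison. No figure is stated for the 2SLS analysis, so the rates below are assumptions unless marked otherwise.

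**Step 1: what 2SLS identifies.** Let *a* be the share of always-users and *c* the share of compliers, with nobody who uses the tool only when not facilitated. Use is then *a* + *c* in the PCD tool arm and *a* in usual care. With arm as the only instrument, and assignment acting only through use, 2SLS estimates (difference in outcome)/(difference in use). Always-users contribute equally to both arms and cancel, so this is the complier effect.

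**Step 2: what TOT would be.** With 1:1 allocation the treated fraction is (*a* + *c*)/2 + *a*/2 = *c*/2 + *a*. The share of always-users among the treated is *s* = *a*/(*c*/2 + *a*), and TOT = *s* × (always-user effect) + (1 − *s*) × (complier effect).

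Inputs: *c* = 0.50 (assumed); *a* = 0.047 (the 2018 adoption rate under PCD Tool Arm, taken as a stand-in for usual-care use) or 0.20 (assumed); complier effect 0.4 SD (assumed).

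| *a* | *s* | 2SLS | TOT if always-users gain 0.8 SD | TOT if always-users gain 0.2 SD |
|---|---|---|---|---|
| 0 | 0 | 0.40 | 0.40 | 0.40 |
| 0.047 | 0.047/0.297 = 0.158 | 0.40 | 0.4 + 0.4 × 0.158 = 0.46 | 0.4 − 0.2 × 0.158 = 0.37 |
| 0.20 | 0.20/0.45 = 0.444 | 0.40 | 0.4 + 0.4 × 0.444 = 0.58 | 0.4 − 0.2 × 0.444 = 0.31 |

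Simulation with N=250 and 2,000 replicates agrees for the 0.8 SD column: mean 2SLS 0.401 and 0.404, TOT 0.463 and 0.578. The gap can go either way and vanishes if both groups benefit equally.

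**Step 3: why it is not per-protocol.** With an assumed correlation of ±0.3 between use and outcome and a true effect of 0.4 SD, a per-protocol contrast averaged about 0.15 to 0.66, while 2SLS stayed near 0.40.

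**Step 4: the standard error of a hand-run second stage.** With estimate *b*, actual use *X* and predicted use *X̂*, the correct residual is *u* = Y − *bX* (intercept omitted). Ordinary output uses Y − *bX̂* = *u* + *bv*, where *v* = *X* − *X̂*. Its variance is Var(*u*) + *b*²Var(*v*) + 2*b*Cov(*u*,*v*). The error is zero when *b* = 0 and can take either sign otherwise.

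Hand check at *a* = 0.20, *c* = 0.50, *b* = 0.8, Var(*u*) = 1, no confounding: Var(*v*) = (0.7 × 0.3 + 0.2 × 0.8)/2 = 0.185, and the ratio is √(1 + 0.64 × 0.185) = 1.06. Simulation gave 1.05.

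Two sets of simulations at N=250:
- Always-users 4.7% to 20%, compliers 50% to 70%, effect 0 to 0.8 SD, confounding −0.3 to 0.3: ratio of ordinary to correct SE 0.98 to 1.12, coverage of the ordinary 95% interval 94% to 97%.
- Use 5% versus 60%, effect 0.4 to 1.0 SD, confounding −0.4 to 0.4: ordinary SE 0.222 to 0.265 against about 0.230, that is about −3% to +15%, coverage 94% to 98%.

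**Step 5: the test.** Without covariates *X̂* is a linear function of arm, so the ordinary second-stage coefficient and SE are the ITT coefficient and SE, each divided by the difference in use. The t statistics are identical (simulated difference below 1e-12).

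**The case against.** The strongest reply is that the substance is already right. The estimator is named as 2SLS, the quoted second-stage sentence is a textbook description, and the correct term (LATE) appears in the text. ITT is primary. At the only documented use rate, 4.7%, the TOT–LATE gap is small even when always-users gain twice as much: 0.46 against 0.40. All of that stands and limits the size of the point. It does not remove it, because the text states that 2SLS will deliver TOT, and the protocol's own expectation of crossover makes that untrue in general.

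Four stronger readings are tempting, and the documents do not support them.

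- **That the protocol commits to wrong standard errors.** It does not. The second-stage description and the GLM/MIXED sentence are separate, and neither says how the 2SLS standard errors are obtained. The words on all aims allow a hand-run second stage but do not prescribe one.
- **That a confounded per-protocol comparison will be run.** None is planned. The 0.15 to 0.66 range shows why the label misleads and is not a forecast of this trial's bias.
- **That the main result is at risk.** The objectives do speak of users and nonusers, so 2SLS matters for interpretation, but the primary inference is ITT.
- **That the causal claim fails because facilitation acts directly.** Under Enrollment Process for PCD Tool Facilitation, "the study team member will review the types of" stories to share. That is instruction in filling in the tool, and an email link alone is one of the listed facilitation types. A direct effect of staff contact and reminders is possible. So is exposure through the paper form used for those without email. With a single instrument this cannot be tested directly, so being untested is no fault. An assumed direct effect of 0.10 SD over an assumed 55-point difference in use would add 0.10/0.55 = 0.18 SD, but neither figure is in the documents.

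**Conclusion.** The point holds for the estimand. The protocol names TOT and equates it with LATE and per-protocol, while its own description of usual care makes 2SLS an estimate of the complier effect only. How far TOT and LATE differ depends on the share of always-users and on how their benefit compares with that of compliers. In the examples TOT runs from 0.31 to 0.58 against a 2SLS value of 0.40, and there is no difference if benefits are equal or always-users are absent. These figures rest on an assumed 50% compliers and assumed effects; only the 4.7% comes from the document.

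The standard-error part is conditional and modest. If the second stage is run as an ordinary regression, the error is about −3% to +15% under the assumed ranges, coverage stays at 94% to 98%, and the test of no effect is that of ITT. The causal conclusion also needs its condition stated, namely that assignment affects outcomes only through tool use. No finding is made that this condition is violated.

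**What to change.** - In Analysis and Study Design Innovations, name the estimand the complier average causal effect (LATE), and delete TOT and per-protocol as synonyms.
- Limit the conclusion about the causal effect of tool use to compliers, and make it conditional on assignment acting only through tool use.
- State that standard errors and intervals come from a 2SLS routine or a bootstrap of both stages, in a form that respects provider clustering (for example by resampling providers), and not from ordinary second-stage GLM or MIXED output.
- Optionally, add a short sensitivity table for assumed direct effects of facilitation.

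The cost is a few sentences and one changed procedure call or bootstrap. No new data are needed and the ITT analysis stays as it is. The protocol reports that analysis was completed in May 2020, so the place to make the correction is the two planned outcome manuscripts, rerunning the second stage only if it was fitted by hand.

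### The missing value analysis is said to determine MAR versus MNAR, which observed data cannot do, and imputation resting on MAR follows whatever it shows

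*Protocol article*

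**What the plan says.** All references are to the protocol article. Under Analysis, the missing value analysis is run on the final data set "to determine whether data were missing completely at random, missing at random, or missing not at random". The text goes straight on to the method: "we will use multiple imputation by chained equations to fill in missing data stratified by race". On the content of the imputation model it says: "The imputation algorithm will include participant demographics and clinical characteristics". The choice of imputation is not made conditional on the result of the missing value analysis, and the MAR assumption is not named.

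The same section makes intention-to-treat the primary analysis, in which "every randomized participant is analyzed in the group to which they were randomly assigned". The sample size section expects appreciable loss: "To account for up to 20% potential dropout over time, we aim to enroll 300 participants".

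Under Data Collection, the CAT is measured only after the visit. The baseline communication measure is a different instrument, the CG-CAHPS communication composite.

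**The concern.** MAR and MNAR differ in whether, given what was observed, the chance of a value being missing still depends on the value itself. That value is not in the data set, so no analysis of the final data set can settle the question. The article presents it as something the data will settle.

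The next step does not fit the first. If the check were read as finding MNAR, the stated imputation would not match that finding. If it were read as finding MAR, the report would claim a verification that had not taken place.

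This bears on the primary outcome. A participant without a postvisit survey has no earlier CAT value and enters the intention-to-treat analysis through imputation. Whether someone answers a survey about a visit could plausibly depend on how the visit went. Non-response could also differ by arm, since the PCD arm has extra staff contact before the visit (Enrollment Process for PCD Tool Facilitation).

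**Working it through.** **1. The plan's own figures.** Two equal arms of n, two-sided α = .05, power ≈ Φ(d·√(n/2) − 1.96).
- Total 200, d = 0.4: 0.4 × √50 = 2.828; 2.828 − 1.96 = 0.868; power 80.7%. The article says 80%.
- Total 250, d = 0.4: 0.4 × √62.5 = 3.162; 3.162 − 1.96 = 1.202; power 88.5%. The article says 88%.

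The stated power reproduces, so 0.4 SD is a fair yardstick. With 20% loss, 300 × 0.80 = 240 evaluable.

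**2. Why the data cannot tell MAR from MNAR.** Suppose 20% of each arm is missing and the observed arm difference is 0.40 SD. Let the unseen PCD-arm scores be lower by δ than an MAR model predicts, and leave usual care as predicted. The true full-sample effect is 0.40 − 0.20 × δ:

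| δ in PCD arm (assumed) | MAR estimate | True effect |
|---|---|---|
| 0 | 0.40 | 0.40 |
| 0.5 SD | 0.40 | 0.40 − 0.10 = 0.30 |
| 1.0 SD | 0.40 | 0.40 − 0.20 = 0.20 |

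The observed values and the pattern of missingness are the same in all three rows, so any test on them gives the same answer. A simulation built this way gave an observed estimate of 0.403 each time, against true effects of 0.401, 0.301 and 0.201.

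**3. Size for the arm contrast.** Inputs: the 20% dropout ceiling (Sample Size Determination and Randomization) and a departure of 0 to 0.5 SD, which is an assumption with no source in the article.

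Shift = (missing share × departure in the PCD arm) − (missing share × departure in usual care).
- One arm only, 20% missing: 0.20 × 0 = 0; 0.20 × 0.3 = 0.06; 0.20 × 0.5 = 0.10 SD. The last two are 15% and 25% of 0.4 SD.
- One arm only, 10% missing: 0.10 × 0.5 = 0.05 SD.
- Both arms, same share and same departure: 0.
- Both arms depart by 0.5 SD, 20% against 10% missing: (0.20 − 0.10) × 0.5 = 0.05 SD.

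**4. Type I error with 240 evaluable.** SE = √(4/240) = 0.129 SD.
- Shift 0: 5%.
- Shift 0.06: 0.06/0.129 = 0.46 SE; P(|Z + 0.46| > 1.96) ≈ 7.5%.
- Shift 0.10: 0.10/0.129 = 0.77 SE; P(|Z + 0.77| > 1.96) ≈ 12.1%.

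**5. What a tipping point would look like.** Holding that SE fixed, with 20% missing and the departure in the PCD arm only:
- An estimate of 0.35 SD has lower limit 0.35 − 1.96 × 0.129 = 0.097 and loses significance at δ = 0.097/0.20 ≈ 0.49 SD.
- An estimate of 0.40 SD has lower limit 0.147 and loses significance at δ = 0.147/0.20 ≈ 0.74 SD.

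**The case against.** Four points can be made for the plan.

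First, a reader might infer that the trial has no MNAR sensitivity analysis, so that a result depending on MAR would go unchecked. The documents do not support that. Only a condensed article is at hand, and sensitivity analyses for missing data are commonly left to the statistical analysis plan or full protocol. What can be said is that no step described in the article examines the assumption. The additional treatment-on-the-treated analysis deals with noncompliance, not missing data.

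Second, a reader might infer that non-response will differ by arm. That is also unsupported. The Usual Care Arm section gives both arms the same postvisit follow-up: up to three email reminders, then a call, with telephone or in-person completion available. The payment of US $25 per completed survey is not distinguished by arm. Differential non-response is a possibility, not a certainty.

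Third, 20% is a ceiling, and the departure used above is assumed and placed in one arm. The range properly starts at 0.

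Fourth, because imputation goes ahead in any case, the faulty sentence does not change the estimator or the primary estimate. Multiple imputation is a conventional primary approach.

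All four stand, and they limit the claim. None rescues the sentence itself. It is an analysis stated wrongly, and no unseen document can make the promised step work.

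**Conclusion.** The point holds in limited form. The article promises a determination that observed data cannot give, then fixes an imputation that as described rests on MAR whatever the outcome. The harm is to interpretation: a report that the mechanism had been determined would lend the primary result a support it does not have. It does not follow that the primary estimate is biased.

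The possible size is 0 to 0.10 SD on the arm contrast, with type I error from 5% to about 12%. This assumes 20% missing, 240 evaluable and a departure of 0 to 0.5 SD confined to one arm. It falls to 0 if missing share and departure are equal in both arms. The statement should be corrected, but it is not a flaw in the design.

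**What to change.** - Delete the claim to determine the mechanism. Say instead that missingness will be described by arm, race and baseline variables, and that such a description can give evidence against MCAR only.
- State that the primary analysis assumes MAR given the variables in the imputation model, and that this cannot be tested from the data.
- Unless the statistical analysis plan already has an equivalent, add a delta-adjusted multiple imputation of the CAT. Shift the imputed values (for example from 0 to −0.5 SD, and further if needed) in the PCD arm only, in usual care only and in both. Report the shift at which the conclusion changes.

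The cost is a change of wording and one extra imputation analysis, with no new data. The Results section says the analysis was completed in May 2020, so the correction would be made in reporting, with the added analysis labelled as such.
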